### **Interviews enablers and barriers of participation, sustainability and effectiveness of the training program**

[name], an experienced qualitative researcher with a medical background, with support from a practicing Aboriginal Health Practitioner will conduct the interviews.

Interviews will be conducted face to face or by Zoom. If face to face, participants will be asked if they could arrange a space within their health service or if they would like the study team to arrange a space in public area such as a room in a local library or in another organisation. While all participants will be invited to participate in an interview, we will aim for a maximum of 15 participants given time and feasibility. If there is a choice (based on recruitment), we aim to have representation across geographic locations and service sizes and systems infrastructure, with a mix of AHW/Ps, Aboriginal nurses, and multidisciplinary staff. Participants will be asked permission for the interviews to be recorded. Interviews will be transcribed professionally, and participants will be invited to add or edit their transcript.

### **System assessment**

Sites vary in the systems and infrastructure available to enable and support the management of type 2 diabetes. The importance of assessing these service characteristics and taking them into consideration in interpreting study findings was emphasised in discussions with the Aboriginal Health Council of South Australia in the development of the grant proposal.

Focus groups with the chronic disease team or staff will be conducted to assess the system characteristics of each service. These will be conducted face to face or via zoom. Focus groups will occur at a time suitable to the service, within the first 12 months of trial commencement. Two researchers will conduct the focus groups. The ACIC will be used to inform the focus of discussions and system assessment. Participants will be provided with the assessment scale prior to the focus group. The focus groups will not be recorded. Staff who participated will be given the opportunity to review the assessment and provide feedback which will be added.

### **Medical record review (quality of diabetes care and diabetes clinical outcomes)**

Negotiating collaborative agreements with sites prior to study implementation includes the sites agreeing or not agreeing to provide de-identified data from their electronic patient management system (PMS) on their diabetes clients, as defined in section 10.d. As the sites do not all use the same type of PMS, the study will work with the clinic/data manager at each site to determine the best data extraction method for their individual electronic PMS. This will likely require a data extraction report to be written (coded) by the data manager from the site or by the PMS vendor (e.g., Medical Director, Communicare). Data extraction software may also be utilised, such as CAT Plus from PENCS, which compatible with the majority of PMS across Australia. All identifiable data extracted from a PMS using CAT Plus is securely stored within the service and not moved offsite.

The data extraction will be run onsite by an appropriate staff member (as identified by the health service) and saved as a CSV file. The extracted data will be de-identified. The CSV file will be password protected and sent by secure email to the Study Manager.

The study will support the services with the data extraction, as required, including providing reimbursement for their time.

The number of times electronic medical record data is collected will be negotiated with each individual service - ideally, at the beginning, midway and at the end of the project (namely, at T1, T4 and T6(Figure 4)).

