## Time period for recruitment

**Training program:** Three months is allocated to recruit participants.

**Interviews barriers and enablers:** Four weeks allocated to recruit participants inclusive of the last two weeks of the training program.

**Systems assessment:** Services will confirm their participation in the system assessment during the development of the Collaborative Agreement. This will be revisited during the first 12 months of the project at the time we are arranging to do the system assessment. Services can decide then or at any point that they do not want to be involved in the system assessment.

**Medical record review:** Services will confirm their participation in the medical record review during the development of the Collaborative Agreement. This will be revisited during the first 12 months of the project at the time we are arranging to collect data. Services can decide then or at any point that they do not want to be involved in the medical record review.

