## **Data collection timepoints for secondary outcomes**

1. Peer Support Network satisfaction survey: This will be collected monthly after each Peer Support Network Meeting for a total of 29 months post-baseline.
2. Interviews of enablers and barriers to participation: this will be undertaken during:
  - T2 with Group A (8.5 Months post-baseline), and
  - T4 with Group B (post group B undertaking the intervention at 17 months from baseline).
3. Medical record review: Quality and Outcomes of diabetes care: This will be undertaken during:
  - T1 - (6 Months Post Baseline Group A & B)
  - T4 - Measure effect of training program (PSN, Online Modules, Onsite Support) on group B post group B undertaking the intervention at 17 months from baseline (data collected on both group A & B).
  - T6 - Sustainability of effect of training program on group A 29 months post-baseline, and group B 12 months post commencement of intervention.
4. Service systems assessment - Health Service Characteristics (through focus groups): This will be undertaken once during the study between months 3 and 12 from the start of the study.

[figure not shown]

Figure 4: Data collection timepoints

| Category                        | Description                                                                                                                                         | Validated tool                                        | Number of variables | When or Timeframe                                            | How                                                                  | From whom                                                                                          |
|---------------------------------|-----------------------------------------------------------------------------------------------------------------------------------------------------|-------------------------------------------------------|---------------------|--------------------------------------------------------------|----------------------------------------------------------------------|----------------------------------------------------------------------------------------------------|

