|                                 | Diabetes management skillm (foot check)                                                                                                             | Research team developed                               | 10                  | T0, T1, T2, T3, T4, T5, T6                                   | RedCap                                                               | All participants                                                                                   |
| Secondary Outcomes              | Evaluation of Peer Support Network                                                                                                                  | Research team developed                               | 9                   | Monthly after each PSN                                       | RedCap                                                               | Aboriginal Health Workers and Practitioners                                                        |
|                                 | Enablers and barriers of participation, sustainability and effectiveness of the training program                                                    | Research team developed                               | up to 12            | Once during the study at T2 with Group A and T4 with Group B | Semi-structured interview - face to face or zoom                     | A cross section of participants from each discipline; 3 to 5 with a total of up to 15 participants |
|                                 | Diabetes patient behaviour and clinical outcomes                                                                                                    | Assessed against RACGP evidence-based care guidelines | up to 8             | Jan 2018 - 12 month post training intervention (T1, T4, T6)  | Retrospective electronic data extraction                             | Electronic medical records of clients with diabetes in each site                                   |
|                                 | Quality of diabetes care                                                                                                                            | Assessed against RACGP evidence-based care guidelines | up to 35            | Jan 2018 - 12 month post training intervention               | Retrospective electronic data extraction                             | Electronic medical records of clients with diabetes                                                |

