## **Secondary Outcomes**

Provision of evidence-based care and patient biomedical outcomes will be summarised using counts, means and percentages and differences between time collection points reported. Patients will be stratified by for example, age, gender, diabetes type and existing comorbidities.

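### The record review schedule is firm in one section and negotiable in another, and the planned differences between time points are not tied to the same services, so a change in contributing services could be reported as a change in care.

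*Protocol*

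**What the plan says.** Four places in the protocol bear on this.

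- **Section 10.c, Data collection timepoints for secondary outcomes.** "Medical record review: Quality and Outcomes of diabetes care: This will be undertaken during" is followed by T1, T4 and T6 (6, 17 and 29 months after baseline). Nothing qualifies it. In Table 3 the row on patient behaviour and clinical outcomes repeats the three points. The quality-of-care row gives only a date range starting in January 2018.
- **Section 10.c, Medical record review.** "The number of times electronic medical record data is collected will be negotiated with each individual service", and T1, T4 and T6 are described as the ideal. The collaborative agreement "includes the sites agreeing or not agreeing to provide de-identified data", so joining the review is optional.
- **Section 10.a, Time period for recruitment.** "Services can decide then or at any point that they do not want to be involved in the medical record review".
- **Section 11.a, Secondary Outcomes.** Evidence-based care and biomedical outcomes "will be summarised using counts, means and percentages and differences between time collection points reported". The only stratifiers named are patient characteristics, such as age, gender, diabetes type and comorbidities. Service is not among them.

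Section 13.a adds that each service is offered its own aggregated results and that all services receive combined results of the audits.

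**The concern.** Two sections describe the same data collection with different force: one as a schedule, the other as an aim to be bargained over service by service. This matters for the analysis because the reported quantity is a difference between time points. A service that supplies T1 and then stops can enter only one side of that difference. Its own change cannot be measured, and its absence alone can move the combined figure.

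Better quality of care and better patient biomedical outcomes are the longer-term part of the hypothesis (section 4) and belong to objective 2 (section 3). The request for a waiver of consent (section 14.c) rests on using these records to judge whether the training works. Section 10.c (System assessment) says that sites vary in systems and infrastructure for managing type 2 diabetes. The record review section adds that they use different patient management systems and will probably need extraction reports written for them. Loss related to a service's capability is therefore plausible, although the protocol does not establish it.

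**Working it through.** **The texts side by side.** The protocol gives no sample size, target difference or error rate for the record review, so there is no figure of its own to reproduce.

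1. The timepoints section and the record review section name the same three points but differ on whether they bind.
2. The right to leave does not contradict a fixed schedule. It does mean that incomplete series are foreseen.
3. The analysis section restricts no difference to services present at both ends.

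**What creates a mismatch.** A service that never joins is absent at every point and causes none. A service that skips T4 but extracts at T6 may still cover some of the gap, because Table 3 makes the extraction retrospective from January 2018. A service that leaves after T1 or T4 supplies nothing later, and that is the case that matters.

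**Illustration 1: continuous spread between services.** Assumptions: 17 services at T1 (section 14.c speaks of a potential 17), equal weights, an indicator whose between-service SD *s* is 10 to 15 percentage points and normally distributed, and no true change in any service. The false change is the mean of the *n* retained services minus the mean of all 17.

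- *Random loss.* SD = s × √(1/n − 1/17). With 5 lost, n = 12: √(0.0833 − 0.0588) = 0.157, giving 1.6 to 2.3 points, centred on zero.
- *The five weakest leave.* By simulation, the mean of the lowest 5 of 17 standard normal values is about −1.112. The shift is (5/12) × 1.112 × s = 0.463s, or about +4.6 to +7.0 points.
- *Loss correlated 0.5 with service level.* Half of that: about +2.3 to +3.5 points.

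With 2 lost (n = 15), the random SD is 0.089s, or 0.9 to 1.3 points. If the two weakest leave, the shift is (2/15) × 1.556 × s, or 2.1 to 3.1 points. At correlation 0.5 it is about 1.0 to 1.6 points.

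**Illustration 2: two kinds of service.** Eight services at 70%, nine at 50%, equal size, no true change.

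| Lost after T1 | Later combined value | Shift from (8×70 + 9×50)/17 = 59.4% |
|---|---|---|
| 4 low | (8×70 + 5×50)/13 = 62.3% | +2.9 points |
| 4 high | (4×70 + 9×50)/13 = 56.2% | −3.3 points |
| 2 of each | (6×70 + 7×50)/13 = 59.2% | −0.2 points |

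With 60% against 50%, losing 2 to 6 low services gives +0.6 to +2.6 points. With 80% against 40%, it gives +2.5 to +10.3 points.

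**After the fix.** If each difference uses only services with data at both ends, the part due to a change of services is zero by construction in every scenario.

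**The case against.** The strongest reply is that the analysis section is silent rather than wrong. It does not say that results are pooled. Section 14.c says client data are analysed in aggregate at the service level, and section 13.a offers each service its own results. Both are compatible with a within-service comparison. How incomplete series enter a descriptive difference could be settled in a statistical analysis plan, which is not available here. The outcomes are secondary and descriptive, with no test attached in that section, so no primary inference is affected. The lost services and the spread between them are assumed, and balanced loss does almost nothing.

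Much of this stands. A reader might infer that the protocol commits to a pooled comparison and that its differences would compare different sets of services. The documents do not support that: the mismatch arises only if services use the option to stop or to supply less, and the method of combining is not stated.

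Two things survive. Whether the three time points are required or a target is a data-collection commitment made in each service's collaborative agreement, and a later analysis plan cannot recover data that a service never agreed to give. Combined results are promised, while the only stated analysis leaves a service that stops early free to count on one side of a difference.

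**Conclusion.** The point holds in limited form. The two parts of section 10.c disagree on whether T1, T4 and T6 are fixed. The analysis wording does not prevent a change in contributing services from being reported as a change in care. For 5 of 17 services lost, the artefact ranges from noise with SD of about 1.6 to 2.3 points under random loss to a shift of about 5 to 7 points if the weakest five leave. It has a direction only when leaving is related to care level. These sizes rest on assumed values for the number of services, their spread and the pattern of loss. They show what could happen and do not predict it. The primary outcomes are untouched.

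**What to change.** 1. In section 10.c, make the timepoints section and the record review section agree: state whether T1, T4 and T6 are a required schedule or a target, and carry the same wording into Table 3 and the collaborative agreements.
2. In section 11.a, state that each difference between time points is computed within service, only over services with data at both points, and then combined across services. Report the number of services behind each difference.

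The cost is wording, with no new data items. The downside is that a service with only one time point leaves the change estimate, so the result describes continuing services. The number of services, reported beside each difference, shows readers how far that limits it.

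One apparent shortcut should be avoided: taking every period from a service's latest extraction. Sections 8 and 10.d set client eligibility at the time of record review, including at least two attendances in the preceding 12 months. Earlier periods drawn that way would be limited to clients still attending later, which would replace a change in services with a selection of clients.

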#### **d. Access to existing data**

| Name/Description of data                               | Electronic Medical Records                                                                                                                                                                                                                                                                                                                                                                                                                                                                                                                                                                                                                                                                         |
|--------------------------------------------------------|----------------------------------------------------------------------------------------------------------------------------------------------------------------------------------------------------------------------------------------------------------------------------------------------------------------------------------------------------------------------------------------------------------------------------------------------------------------------------------------------------------------------------------------------------------------------------------------------------------------------------------------------------------------------------------------------------|
| Data Custodian                                         | SA Health Primary Health Care Sites - Watto Purrunga (Muna Paiendi, Wonggangga Turtpandi), Aboriginal Family Clinic (Noarlunga, Clovelly Park), Yorke & Northern LHN (Point Pearce Port Pirie), Riverland Mallee Coorong LHN.                                                                                                                                                                                                                                                                                                                                                                                                                                                                      |
| Agency Type                                            | State government Aboriginal primary care service                                                                                                                                                                                                                                                                                                                                                                                                                                                                                                                                                                                                                                                   |
| Data Collection Format                                 | De-identifiable                                                                                                                                                                                                                                                                                                                                                                                                                                                                                                                                                                                                                                                                                    |
| Variable                                               | Justification                                                                                                                                                                                                                                                                                                                                                                                                                                                                                                                                                                                                                                                                               |
| Health service level                                   | To provide a basic description / service context for each service.                                                                                                                                                                                                                                                                                                                                                                                                                                                                                                                                                                                                                          |
| Number of regular clients                              | Defined as 3 or more visits in the previous 2 years. This will become the denominator for the proportion of clients with diabetes within a service.                                                                                                                                                                                                                                                                                                                                                                                                                                                                                                                                         |
| Number of regular and transient clients on a care plan | 
The number of current/regular and the number of transient Aboriginal clients, registered with the following conditions, including the number in each category and disease group with a current disease-specific care plan.
 
 
• Cardiovascular Disease
 
• Renal Disease
 
• Mental Health
 
• Diabetes
 
                                                                                                                                                                                                                                                                                                          |
| Number of transient clients                            | The number of clients who are defined as a transient client receiving care at the health service. Transience defined as < 2 visits in 12 months.                                                                                                                                                                                                                                                                                                                                                                                                                                                                                                                                         |
| Indigenous status                                      | Proportion of Aboriginal clients using the service of total client population                                                                                                                                                                                                                                                                                                                                                                                                                                                                                                                                                                                                               |
| Episodes of care                                       | The number of episodes of care received by Aboriginal clients in the previous 12 months. An episode of care is defined as a presentation to the health service where a service was provided.                                                                                                                                                                                                                                                                                                                                                                                                                                                                                                |
| Client level                                           | 
Eligibility criteria: People with diabetes who have attended the participating health service and who fulfil the following criteria at the time of record review meet the following criteria:
 
 
• Both males and females who aged 18 years and over;
 
• identify as Aboriginal or Torres and Strait Islander people;
 
• have a confirmed diagnosis of T2DM and/or a HbA1c <math>\geq 6.5</math> mmol/L;
 
• have attended the health service at least twice in the preceding 12-month period;
 
 
Those who meet the eligibility criteria become the study population in which the below variables are extracted.
 |
| Client ID                                              | Service unique record ID created and provided by the health service so that no identifying data is provided to the study team                                                                                                                                                                                                                                                                                                                                                                                                                                                                                                                                                                      |
| Month & Year of Birth                                  | To estimate age                                                                                                                                                                                                                                                                                                                                                                                                                                                                                                                                                                                                                                                                                    |

|                                                                                                                                                                                                                                                                                                                                                                                                                                                                                                              |                                                                                                                                       |
|--------------------------------------------------------------------------------------------------------------------------------------------------------------------------------------------------------------------------------------------------------------------------------------------------------------------------------------------------------------------------------------------------------------------------------------------------------------------------------------------------------------|---------------------------------------------------------------------------------------------------------------------------------------|
| Sex                                                                                                                                                                                                                                                                                                                                                                                                                                                                                                   | To examine gender differences                                                                                                         |
| Ethnicity                                                                                                                                                                                                                                                                                                                                                                                                                                                                                             | To identify Aboriginal status                                                                                                         |
| GP Management Plan                                                                                                                                                                                                                                                                                                                                                                                                                                                                                    | To calculate number of clients who have a GPMP                                                                                        |
| Team Care Arrangements                                                                                                                                                                                                                                                                                                                                                                                                                                                                                | To calculate number of clients who have a TCA                                                                                         |
| GP Management Plan Review                                                                                                                                                                                                                                                                                                                                                                                                                                                                             | To identify proportion who have had a GPMP review within the recommended timeframe according to evidence-based care guidelines        |
| Diabetic retinal check performed                                                                                                                                                                                                                                                                                                                                                                                                                                                                      | To identify proportion who have had a GPMP review within the recommended timeframe according to evidence-based care guidelines        |
| Diabetic foot check performed                                                                                                                                                                                                                                                                                                                                                                                                                                                                         | To identify proportion who have had a foot review within the recommended timeframe according to evidence-based care guidelines        |
| Absolute CV risk assessment                                                                                                                                                                                                                                                                                                                                                                                                                                                                           | To identify proportion who have had a CV risk assessment within the recommended timeframe according to evidence-based care guidelines |
| BMI                                                                                                                                                                                                                                                                                                                                                                                                                                                                                                   | Identify proportion within recommended range                                                                                          |
| Waist circumference                                                                                                                                                                                                                                                                                                                                                                                                                                                                                   | Identify proportion within recommended range                                                                                          |
| Smoking status                                                                                                                                                                                                                                                                                                                                                                                                                                                                                        | Understand proportion of clients with behavioural risk factors                                                                        |
| Physical activity                                                                                                                                                                                                                                                                                                                                                                                                                                                                                     | Understand proportion of clients with behavioural risk factors                                                                        |
| Influenza vaccination up to date                                                                                                                                                                                                                                                                                                                                                                                                                                                                      | Vaccination status                                                                                                                    |
